### Ethics approval

This study has been approved by the Human Research Ethics Committees of Sydney Local Health District (HREC11/CRGH/289) and the University of Western Sydney (H9709).

### Randomisation

Following consent and baseline data collection participants are allocated to the groups using block randomisation. This form of randomisation is recommended for large trials [29] and has been used in a number of recent trials in this research area [21]. A permuted block randomisation scheme with a random mixture of block sizes is used to set the allocation order, stratifying participants by hospital and presence of a dental problem. Block randomisation ensures that the number of participants in each arm of the trial will be evenly balanced [29]. Randomisation of participants is accomplished centrally using an independent computerised service which is accessed via the telephone at the time of recruitment.

Group allocation (IG1, IG2, CG) is represented by coloured stickers concealed in serially numbered opaque randomisation envelopes. After recruitment, baseline data collection and randomisation via telephone, the dental assistant hands over the randomisation envelope to the pregnant women, who then gives it to the midwife. All midwives at each of the hospitals are aware of which group each coloured sticker represents. To maintain allocation concealment and minimise selection bias the dental assistants are unaware of the colour codes and block sizes used for randomisation. In addition, the study investigators are blinded to group allocation. Due to the randomisation method, pregnant women attending on the same day receive different interventions.

To minimise any distress among pregnant women and maintain equipoise [30], oral health promotion material are provided via the dental assistant at recruitment to all trial participants. Women who refuse to participate are also provided with oral health promotional material. It is also possible that women attending the antenatal clinic on the same day might interact with each other which can lead to potential contamination (estimated at <5%) in the study. We are adjusting for this contamination during analysis [31] and have also included an item in the post questionaire asking if they have discussed their particpation in the study with other women attending the antenatal clinic at the same time. Analysis is being undertaken excluding such women.

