#### Referrals

In this group, all pregnant women assessed to be at risk of poor oral health are referred to current dental services (either private, public or health fund) for treatment. The referral letter provided to pregnant women includes a covering letter and a survey/checklist—date of first visit, total number of visits required, treatment completed (item numbers), and dentists contact details—to be completed by the dentists and returned to the study investigators via fax. Information on the survey/checklist is also sought from private dentists whose contact details are provided by pregnant women in the post questionnaire. The checklist helps to assess the uptake of dental services, the common treatment requirements and associated dental costs, all of which are vital information to inform future economic evaluations and subsequent state and national policy in this area.

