##### Intervention group 2 (IG2)

This group receives oral health promotional material at the time of recruitment. This group also receives a **midwifery and dental intervention** (MIOH-DS). The **midwifery intervention** will be similar to Intervention group 1. However, in this group all pregnant women, regardless of whether they are assessed to be at risk of having dental problems or not by the midwife, are referred (referral letter with checklist) to the dentists employed for this study for an initial dental oral assessment (part of the dental intervention). This allows for further testing of the midwifery oral assessment tool and to gather baseline oral health data. Pregnant women who consent are provided vouchers that entitle them to priority access to free oral assessment and treatment by the study dentists at dental clinics in the recruitment hospitals. This service is an extra service created specifically for this study and is co-ordinated by the study team. The voucher is valid for 4 weeks from booking visit date to encourage pregnant women to see the dentist promptly. Pregnant women can make the dental appointment by calling the telephone number provided with the referral letter or contacting the dental assistant in the antenatal waiting room.

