##### Control group (CG)

This group receive oral health promotional material at recruitment. This material focuses on the importance of oral health, good oral health practices (dietary counselling, fluoride use, quitting smoking) and advice on seeing a dentist during pregnancy. They do not receive any intervention until the completion of the trial. At the point of completion, these women are referred to dental services, if required. Figure 2 outlines the design of the MIOH-DS trial which follows the principle of equipoise.

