**Detailed design of MIOH-DS trial.**

### Outcome measures

The following outcome measures—estimates of uptake of dental services, oral health knowledge, quality of oral health, oral health status and birth outcomes are proposed for this trial:

*An estimate of the uptake of dental services* will be obtained from the following sources: the returned checklist; the database of the study dental clinics; data from the post questionnaire, following up all referrals by midwives and at the final dental oral assessment period; contacting private/health fund dentists used by the women (contact details obtained from the post questionnaire and returned checklist).*Oral Health Knowledge* will be assessed using a pre-test and post-test questionnaire (tested in the pilot study) [19] and administered to pregnant women at the recruitment and final dental oral assessment period respectively.*Quality of oral health* will be assessed using the following validated item [37] to be included in the pre and post questionnaire: ‘On a scale of 1–5 where 1= poor and 5=excellent, How would you describe the health of your teeth and mouth?*Oral health status* will be assessed using several measures—gingival inflammation and bleeding, clinical attachment loss, level of plaque and dental caries*.* These measures are to be used at both the dental oral assessments: –Gingival inflammation and bleeding is assessed using The Sulcus Bleeding Index [38] and is used to measure the degree of inflammation and bleeding in the gums;–Clinical Attachment Loss (CAL), measures the degree of CAL (periodontal pocket depth, gingival recession and calculus) and is assessed using a calibrated periodontal probe [39];–Level of plaque is measured using The Approximal Plaque Index [38].–Dental caries will be determined by the Decayed, Missing, Filled Teeth (DMFT) Index [40]. The DMFT index is used to monitor the changes in the various components. If the intervention is successful decayed teeth will have been filled or removed.

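### The article calls the study investigators blinded, yet has them receive by fax the referral checklists that, before the end point, only intervention-arm women carry

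*Protocol article*

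**What the plan says.** All references are to the protocol article.

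- **Randomisation:** "In addition, the study investigators are blinded to group allocation". No exception or time limit is given. The Discussion later lists concealment from researchers among the trial's features.
- **Referrals (IG1):** "all pregnant women assessed to be at risk of poor oral health are referred to current dental services (either private, public or health fund"). Each letter carries a checklist recording the date of first visit, number of visits, treatment items and dentist's contact details, "to be completed by the dentists and returned to the study investigators via fax".
- **Intervention group 2 (IG2):** all women, whatever their assessed risk, "are referred (referral letter with checklist) to the dentists employed for this study". Of the clinic service offered to this arm only: "This service is an extra service created specifically for this study and is co-ordinated by the study team".
- **Control group (CG):** "They do not receive any intervention until the completion of the trial". Referral, if needed, follows completion.
- **Second route to checklist information (Referrals):** "Information on the survey/checklist is also sought from private dentists whose contact details are provided by pregnant women in the post questionnaire". Under Dental intervention, that questionnaire goes to all women, controls included, at 28–32 weeks.
- **Outcome measures:** uptake is estimated from returned checklists, the study clinic database, the post questionnaire, follow-up of midwife referrals, and "contacting private/health fund dentists used by the women (contact details obtained from the post questionnaire and returned checklist").
- **Data analysis:** the analyses are run by staff who do not know the allocation.

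**The concern.** The blinding statement and the fax instruction name the same people. A form that only two of the three arms carry during follow-up shows its recipient that the woman is in one of those two arms.

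Two things are at stake. First, readers will take the blinding claim at face value when they judge the trial. Second, uptake of dental services is the outcome that sets the sample size, and part of it depends on effort: following up referrals and tracing private dentists. If the people doing that work knew the arm, the effort could differ by arm. The article describes no rule that holds it equal.

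**Working it through.** **The plan's own figure.** The point has no stated figure of its own, but the sample size shows how much rests on uptake. The inputs from Sample size are 30% against 50%, two-sided alpha 0.017 and 80% power. With pooled variance and no continuity correction:

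n = [2.387 × √(2 × 0.40 × 0.60) + 0.842 × √(0.30 × 0.70 + 0.50 × 0.50)]² / 0.20² ≈ 124 per group.

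Then 124 / (1 − 0.40) ≈ 207, and 3 × 207 = 621. All three match the article. None of them bears on blinding.

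**Who can generate a returned checklist, and when**

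| Arm | Checklist with a referral letter before the end point | Checklist information via a dentist named in the post questionnaire |
|---|---|---|
| Control | No | Possible, from 28 weeks |
| IG1, at risk | Yes, fax to investigators stated | Possible, from 28 weeks |
| IG1, not at risk | No | Possible, from 28 weeks |
| IG2 | Yes, return implied | Possible, from 28 weeks |

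A checklist that came with a referral letter excludes the control arm. Its sender, a study dentist or an outside dentist, then largely separates IG2 from IG1.

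**Can timing tell the two routes apart?** Women enter before 20 weeks of gestation (Participants and recruitment). The IG2 voucher lasts 4 weeks from booking, so it expires before 20 + 4 = 24 weeks. Urgent IG2 treatment is planned for the second trimester, given as 13–27 weeks. The post questionnaire starts at 28 weeks. A checklist received before 28 weeks therefore cannot come from the questionnaire route and must belong to a referred woman. After 28 weeks, information obtained from a private dentist named in the questionnaire does not by itself reveal the arm.

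**How many women are revealed?** This illustration assumes the article's 50% uptake, every checklist returned, and 124 women per group.

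- IG2: 0.50 × 124 = 62 women.
- IG1: at most 62, because attenders not assessed as at risk carry no checklist.
- For a woman with no referral checklist, the chance that she is a control rises from 1/3 to at most 1 / (1 + 0.50 + 0.50) = 50%. If only 25% of IG1 women had one returned, it would be 1 / (1 + 0.75 + 0.50) = 44%.

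These figures describe how much the investigators could learn. They do not measure bias.

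**The case against.** The strongest reply has four parts.

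1. **The sentence may concern assignment only.** It follows a sentence on allocation concealment and selection bias, and the Discussion speaks of concealment, not blinding. But as written the sentence says blinded, with no limit. If assignment is all that is meant, the wording should say so.
2. **The investigators named in the fax instruction may simply mean the study office.** That is possible in a condensed article. Even so, the two sections use the same term for the recipients and for the blinded people, so the text conflicts as it stands. Likewise, the study team that co-ordinates the IG2 service need not include the investigators; the article also mentions an administrative assistant.
3. **Not every checklist reveals the arm.** This stands. Controls can enter through dentists named in the post questionnaire, and the fax route is explicit only for IG1. For IG2, return is inferred from the checklist sent with the letter and from its later use, under Outcome measures, to judge the dentists' adherence. The IG1 route alone is enough for the contradiction.
4. **No biased outcome assessment is shown.** This also stands. A reader might infer that the people who compile uptake know the arm and that the comparison is inflated. The article names nobody who compiles uptake, and it blinds the analysis staff. That blinding does not cover whoever gathers the data, but a gap in description is not evidence of bias. Nor can a false difference be put in percentage points: the article gives no detection rates by arm. Any better detection in the referred arms would come mostly from the extra sources they have, namely referral checklists and the study clinic database, whoever is blinded.

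**Conclusion.** The point holds as a contradiction between a stated safeguard and a stated procedure. Investigators who receive referral checklists learn that those women are not controls, with certainty for any checklist arriving before 28 weeks, so the unqualified blinding claim fails. Under full return and 50% uptake it fails for about 62 of 124 women in IG2 and at most 62 of 124 in IG1. Fewer returns would mean fewer.

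This rests on reading the investigators in the two sections as the same people, and, for IG2, on its checklists going back the same way. The effect on the uptake comparison cannot be quantified from the article and may be nil. The conflict still merits correction, because the claim is one that readers will rely on and the repair is cheap.

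**What to change.** In Referrals, change the return address to a data office, or to an existing staff member who neither contacts women for outcome data nor assesses outcomes. The administrative assistant is a poor choice, because that role telephones women in all arms about the final assessment, and the post questionnaire may be given in such calls.

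Investigators still need the treatment, cost and adherence items. Pass these on only without arm identification, which means withholding the dentist's details, or after uptake has been coded. Use the same procedure and number of attempts for dentist contacts in all arms. Say also which members of the study team run the IG2 service.

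The cost is a new fax destination and one reassigned task. The small downside is that investigators cannot query checklists directly during the trial.

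If this is not done, limit the Randomisation sentence and the Discussion's reference to researcher concealment to two things: concealment at assignment and blinded analysis staff. That costs only an edit to the wording.

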##### Dental intervention

At the first appointment all the women undergo an initial dental oral assessment that includes medical history, followed by oral mucosal tissue examination, periodontal examination, dental caries examination and denture evaluation. A provisional diagnosis and treatment plan is made for those women having oral health problems. Once the consent for treatment is obtained, subsequent appointments are made in the second trimester to complete all the urgent treatment for women having dental problems. The second trimester (13–27 weeks) is considered a safe period to carry out necessary dental treatment^10^. The completion of treatment will take 1 to 3 additional visits depending on the treatment plan. Women having complex treatment needs such as root canal treatment are referred to the specialist for follow up care and are excluded from the study. After each examination participants are provided oral health education including oral hygiene instructions, brushing and flossing instructions and dietary counselling.

All women in the control group, intervention group 1 and group 2 (whether or not at risk of dental problems) undergo a final dental oral assessment by the study dentists at 28–38 week gestation period, the end point of this study. This examination is similar to the initial dental oral assessment and includes a detailed clinical examination. All women receive reminder cards from midwives followed up by telephone calls from the study administrative assistant to attend their final dental oral assessment. Pregnant women in the control group identified with a dental problem are referred to dental services after pregnancy. A post questionnaire having similar items to the pre questionnaire (demographic data, dental/medical aspects of the women’s health such as uptake of dental services, quality of oral health and post-test oral health knowledge), is administered to all women between 28–32 weeks. Contact details of private dentists who were consulted during pregnancy are also sought in the post questionnaire. The following methods are used to administer the post questionnaires: via the dental assistant/receptionist in the antenatal waiting room, via the midwife during the antenatal visit, over the phone when the final dental appointments are being made and via the study dentists at the final dental appointment.

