### Sample size

Sample size estimation is calculated on the outcome measure uptake of dental services using the assumption that 30% of pregnant women in the control group will access dental services during pregnancy (based on our survey [23] and existing Australian studies [10, 43, 44]. We expect the MIOH (IG1) and MIOH-DS service (IG2) will improve the uptake of dental services. The MIOH intervention is considered successful if at least 50% of the pregnant women in IG1 and IG2 will access dental services during pregnancy, a difference of 20% between the groups. To detect a difference of at least 20% between the groups with a two-sided test of proportions, alpha of 0.017 (three comparisons 0.05/3), and 80% power we determine using a statistical software that we require at least 124 patients in each group. Taking into account 10% attrition (refusal after randomisation-based on the results of our pilot survey) and 30 % loss at the endpoint (based on trials in this area - range 2-30%) [21] we will need to recruit 207 participants in each group.

Sample size was also calculated on the outcome measure oral health status using the assumption that 50% of pregnant women in the control group will have gingival bleeding (based on trials in this area) [21]. A 30% improvement in oral health status is expected in IG1 and IG2 (30% reduction in gingival bleeding). To detect a difference of at least 30% between the groups with a two-sided test of proportions, alpha of 0.017, and 80% power we determine using statistical software [45] that we require at least 52 patients in each group. Taking into account 10% attrition and 30 % loss at the endpoint we will need to recruit 87 participants in each group. Based on these estimations we will require a total of 621 participants for the trial (207 in each group). Interim analyses will be used to re-check the sample size after the first 100 women are recruited.

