### Data analysis

Per-protocol and intention-to-treat analysis will be conducted by staff blinded to the group allocation. Missing data will be coded in the database structure and handled using an appropriate method. Demographic data will be analysed using descriptive statistics. All variables will be examined for normality and appropriate data transformations will be applied. Potential confounders (income, pre-existing oral health conditions, and others) and the impact of the MIOH/MIOH-DS intervention will be examined using univariate and multivariate methods. Regression analysis that take into account the variables of interests to the outcome will be performed. Some of the variables will be considered as exerting fixed effects (e.g. the number of patient groups) while others as random effects e.g. oral health knowledge. The regression models will also include a hospital variable (1–3). Analysis will be conducted for each hospital clinic and if no differences are found, data will be pooled. Pearson’s Chi-square test will be used to analyse the proportion of pregnant women accessing dental services. Oral health status and knowledge outcomes will be analysed using Analysis of Variance and post-hoc procedures. The effectiveness of the oral health education program will be assessed using dependent t-tests.

The sensitivity and specificity of the oral assessment tool using the OHIP-14 as the gold standard will be calculated using odds ratios. For this analysis the total scores using the midwifery oral assessment tool for participants in IG1 and IG2 will be dichotomised as 0=0 (no risk) and 1 to 2=1 (at risk). The total scores for participants using the OHIP-14 in IG1 & 2 will also be dichotomised using the median split as described by Locker et al. [42]. Subjects with an OHIP-14 score of 0–7 will be scored 0 (no risk) and 8–56 a score of 1 (at risk). Sensitivity and specificity will also be calculated using the initial dental oral assessment in IG2 as the gold standard. Analysis of proportions using chi square procedures (two tailed) and confidence intervals will be undertaken to determine sensitivity (true positives), specificity (true negatives), false positives, false negatives, negative and positive predictive values [46].

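### Women who report discussing the trial are to be excluded after randomisation, and the protocol does not confine that exclusion to a secondary analysis

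*Protocol article*

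**What the plan says.** The Randomisation section of the protocol article notes that women of different arms attend the same clinic on the same day and may talk, giving "potential contamination (estimated at <5%) in the study". It then describes two ways of dealing with this:

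- An adjustment: "We are adjusting for this contamination during analysis", with a literature reference for the method.
- An exclusion: an "item in the post questionaire asking if they have discussed their particpation in the study with other women" who attend the clinic at the same time, followed by "Analysis is being undertaken excluding such women".

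Under Dental intervention, the post questionnaire "is administered to all women between 28–32 weeks", which is after allocation and after the booking-visit intervention.

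Under Data analysis, the article states: "Per-protocol and intention-to-treat analysis will be conducted by staff blinded to the group allocation". Neither analysis is called primary, and neither the exclusion nor the contamination adjustment appears there. The Sample size section allows for 10% attrition and 30% endpoint loss, with nothing for this exclusion.

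**The concern.** Randomisation makes the arms comparable as allocated. Removing women for something they did afterwards keeps that comparability only if the removal is unrelated to allocation and outcome. There are three reasons to doubt that here.

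1. **Allocation may affect the answer.** Women in IG2 receive vouchers, priority access and free assessment and treatment. IG1 women receive a midwife assessment and, if at risk, a referral. Control women receive printed material only. The amount there is to talk about differs, so the share and type of woman excluded could differ by arm.
2. **The item measures talking, not contamination.** Contamination is exposure of a woman to another arm's intervention. An intervention woman who talked still received her allocated care, yet the rule removes her.
3. **Only responders can be excluded.** A woman who talked but did not return the questionnaire is not identified. This matters chiefly for uptake, which also has other sources (checklists, clinic database, dentists). Post-test knowledge comes from the questionnaire itself, so non-responders have no knowledge outcome in any case.

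At stake is whether the main comparison of uptake, oral health and knowledge is the randomised one.

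**Working it through.** **Inputs from the Sample size section:** uptake 30% in control and 50% in each intervention arm; two-sided test of proportions; alpha 0.017; 80% power; 124 evaluable and 207 recruited per group. **From the Randomisation section:** contamination below 5%. The share of women who will report talking is not given.

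**Step 1. Reproduce the plan's figure.** With pooled variance under the null and p̄ = 0.40:

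n = [z(1−0.017/2)·√(2·0.40·0.60) + z(0.80)·√(0.30·0.70 + 0.50·0.50)]² / 0.20²
= [2.387·0.6928 + 0.842·0.6782]² / 0.04 ≈ 124.

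Power at 124 is 80.1%. Recruitment is 124/(1 − 0.40) = 206.7, so 207. Both stated figures reproduce.

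**Step 2. Power after exclusion.** Power = Φ{[0.20·√n − 2.387·0.6928] / 0.6782}.

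| Excluded per arm | n left of 124 | Power |
|---|---|---|
| 0% | 124 | 80.1% |
| 3% | 120.3 | 78.7% |
| 5% (upper bound for contamination) | 117.8 | 77.7% |
| 10% (assumed) | 111.6 | 75.1% |
| 20% (assumed) | 99.2 | 69.1% |

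At 5% the loss is 80.1 − 77.7 = 2.4 points. If the 10% and 30% losses act in sequence, 207 × 0.9 × 0.7 ≈ 130 are evaluable (82.2% power). Removing 5% then leaves 123.5 and 79.9%.

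**Step 3. Power if nobody is excluded and contamination stays in.** Suppose 5% of control women take up care at the intervention rate. Control uptake becomes 0.30 + 0.05 × (0.50 − 0.30) = 0.31. Power for 31% v 50% with 124 per arm is 75.0%, which is below the 77.7% with exclusion.

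**Step 4. Bias from exclusion.** Suppose there is no true effect and uptake is 50% in both arms. Let f be the share excluded and r the uptake among those excluded. Uptake in the women who remain is (0.50 − f·r)/(1 − f). All f and r below are assumptions.

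| f: intervention v control | r: intervention v control | Remaining uptake | False difference |
|---|---|---|---|
| 10% v 5% | 30% v 60% | 52.2% v 49.5% | +2.7 points |
| 10% v 5% | 60% v 30% | 48.9% v 51.1% | −2.2 points |
| 10% v 5% | 80% v 80% | 46.7% v 48.4% | −1.8 points |
| 20% v 10% | 30% v 60% | 55.0% v 48.9% | +6.1 points |
| 20% v 10% | 60% v 30% | 47.5% v 52.2% | −4.7 points |

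The sign depends on who talks in each arm, which cannot be known in advance. A larger sample would not remove this.

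**The case against.** A reader might infer that the exclusion contradicts intention-to-treat. The text does not establish that. Data analysis plans both intention-to-treat and per-protocol analyses, and the Randomisation section does not call the analysis with exclusion the main one. It can be read as an additional or per-protocol analysis alongside the adjusted one, which is an ordinary pair. The full plan, not shown here, may say so. This stands, and the finding is limited to the passages being unreconciled. It does not excuse the sentence itself, which states a rule without limit. Read as written, it could govern the primary comparison.

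A reader might also infer that the exclusion seriously lowers power. It does not on the protocol's own figure: the loss is at most about 2.4 points, and near nil if the losses act in sequence. Leaving 5% contamination in costs more (75.0% v 77.7%). The case for keeping all women therefore rests on validity, not power. Larger losses need an assumed talking rate well above the contamination figure.

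Finally, a reader might infer a known bias. For example, if 20% of IG2 women talk, 70% of those take up care, and only they are dropped, IG2 uptake falls to (0.50 − 0.20 × 0.70)/0.80 = 45%. Both inputs are assumed and the control arm is left untouched. The documents support only that exclusion rates could differ by arm and that bias could follow. The item is also limited to women attending at the same time, which may keep the number small.

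**Conclusion.** The point holds in limited form. The Randomisation section fixes an exclusion on self-reported behaviour after allocation, does not confine it to a secondary analysis, sets it beside a separate adjustment, and is not reconciled with the analyses listed under Data analysis. If followed as written, the resulting comparison is not the randomised one.

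The size of any bias cannot be fixed from the documents. The illustrations, from −4.7 to +6.1 points against a planned difference of 20 points, rest wholly on assumed exclusion rates and uptake, and show only that either direction is possible. The effect on power is minor at the stated contamination level.

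**What to change.** In the Randomisation and Data analysis sections:

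- State that the primary comparison is intention-to-treat, with every randomised woman analysed in her allocated arm whatever she reports about discussing the trial.
- Report the proportion who report discussion, by arm, among those who answered the item.
- Label the analysis excluding these women, and the contamination adjustment, as sensitivity (or per-protocol) analyses, and say how the two relate.

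This takes a few sentences and no new data, and should be settled before unblinding. The price is slight dilution from contamination left in: about 75% power for uptake if control uptake rises to 31%. No change in sample size is needed on this account. The fix restores the allocated groups but does not by itself make the estimate unbiased, since the plan also allows for 10% attrition and 30% endpoint loss.
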